#### ***1.4.3. Conclusions***

Comparative physicochemical and non-clinical studies as well as the Phase I study of the PK, tolerability, and safety in healthy volunteers did not show any statistically significant differences between BCD-057 and Humira®. Thus, it is expected that, in this study in patients with moderate-to-severe plaque psoriasis, BCD-057 will demonstrate the efficacy, safety, immunogenicity, and PK similar to those of the originator.

The risks of adverse events have been thoroughly investigated. The treatment with adalimumab very rarely results in severe or life-threatening reactions and is expected to have low immunogenicity. At the same time, multiple international clinical studies of TNF $\alpha$  blockers and the wide clinical experience gained with Humira® suggest the benefit for the patients participating in the study. In

adalimumab clinical studies, a PASI 75 response was achieved by 80% patients, a reduction in sPGA to score 0 or 1 was achieved by up to 70%, the BSA decreased, and the patients' quality of life improved. Thus, the total risk/benefit ratio for subjects participating in this clinical study is considered favorable.

### ***1.5. Description and justification of route of administration, doses, dosing regimen and treatment course***

#### ***1.5.1 Design description and justification***

This is a double-blind, randomized clinical study of the efficacy and safety conducted in two parallel arms.

The double-blind design is used to minimize the bias during the physician's and patient's assessment of treatment results, minimize systemic errors, and, therefore, to improve the validity of study results.

Stratification procedure ensures that any factors that can affect treatment results are uniformly distributed between the study arms, thus allowing investigators to attribute differences in responses directly to the investigational product. Some authors suggested a relationship between the patient's body weight (or BMI) and response to adalimumab [2, 10]. Similar trends were reported for other biologics used for the treatment of psoriasis [9, 10]. With the current data and the fact that the adalimumab dose is not titrated depending on the patient's body weight, all included patients will be stratified by body weight ( $< 80$  kg /  $\geq 81$  kg). The M02-528 study also used stratification by body weight [1].

In addition, the patients will be stratified according to the prior exposure to antibodies for the treatment of psoriasis (experienced / naive), PASI score ( $< 20$  /  $\geq 20$ ), and the presence of psoriatic arthritis (no / yes).

The active comparator allows making an objective comparison between the investigational products because treatment conditions were absolutely similar in both arms.

BCD-057 is a biosimilar of Humira®, which demonstrated its clinical efficacy and safety in large clinical trials and in a post-marketing setting. Humira® is used as a reference drug in this study. The choice of the reference drug completely meets the EMA's guideline on similar biological medicinal products containing monoclonal antibodies (EMA/CHMP/BMWP/403543/2010).

The main study hypothesis is that BCD-057 is equivalent to the original Humira®. According to the EMA's guidelines (EMA/CHMP/BMWP/403543/2010), this hypothesis is the most appropriate one to confirm the similarity between a biosimilar and the originator in a clinical study.

Each patient will be observed for 55 weeks (about one calendar year). This time will allow assessing not only the primary endpoint (the proportion of patients achieved PASI 75 at Week 16), but also analyzing long-term efficacy indicators and thoroughly investigating the immunogenicity and safety of BCD-057 vs. the originator in patients with moderate-to-severe plaque psoriasis. This study duration is recommended by the EMA's guideline on clinical investigation of medicinal products indicated for the treatment of psoriasis (EMA/CHMP/EWP/2454/02).

The primary endpoint in this study is the proportion of patients with a PASI 75 response at Week 16. This is a sensitive indicator for patients with moderate-to-severe plaque psoriasis. This measure is widely used in clinical studies to assess the efficacy of medicinal products for the treatment of psoriasis and is recommended by the EMA's guideline as the primary endpoint to assess the efficacy of medicinal products indicated for the treatment of psoriasis (EMA/CHMP/EWP/2454/02). The time of the primary endpoint evaluation was chosen based on the PK of adalimumab (time to steady state) and is appropriate to evaluate the drug effects according to the EMA's guideline. The use of PASI alone may be not enough for the comprehensive efficacy assessment, so the clinical course of psoriasis in the study will be assessed in detail by analyzing the changes in the BSA, changes in the sPGA score, changes in the absolute PASI scores, and other indicators. This agrees with the EMA's Guideline on *Clinical Investigation of Medicinal Products Indicated for the Treatment of Psoriasis* (EMA/CHMP/EWP/2454/02).

This study is to compare the pharmacokinetics of BCD-057 and Humira® in a limited patient population (90 subjects from each study arm, 180 subjects total). This investigation is necessary to demonstrate that pharmacokinetics of these drugs is similar not only in healthy volunteers but in psoriasis patients as well (who may differ from healthy subjects in terms of adalimumab PK). In patients with plaque psoriasis, adalimumab is used for a long time, so it is important to study its PK parameters at steady state – when an equilibrium between the intake of the drug and its elimination has been achieved. Adalimumab fully exerts its clinical effects when reaches the steady state concentration. In addition, steady-state PK allows predicting how rapidly the serum levels of the active ingredient decrease is the patient misses a dose or discontinues the drug.

It is known that the time to steady state equals 3 to 5 half-life periods of adalimumab. For adalimumab, the average half-life is 2 weeks, varying from 10 to 20 days [8]. Thus, the maximum time to steady state will be 100 days or 14.3 weeks ( $20 \times 5 = 100$ ). According to literature data, adalimumab concentrations reach the steady state in 12 to 16 weeks. Blood specimens will be

---

 Adalimumab M04-688 Pharmacokinetic Report

[http://www.abbvie.com/assets/research/clinical-trials-data-and-information-sharing/synopses/adalimumab\\_M04-688.pdf](http://www.abbvie.com/assets/research/clinical-trials-data-and-information-sharing/synopses/adalimumab_M04-688.pdf)

taken at frequent intervals after the 9th injection of adalimumab (at weeks 15 and 16), and thus the PK of BCD-057/Humira® will be studied at steady state.

In the second period of the study, some patients will be crossed over from one drug product to another. After completing Week 24 and all appropriate assessments, one half of patients from the Humira® arm will be switched to BCD-057. The rest of patients who were originally randomized to receive Humira® will continue the treatment with Humira®.

The same study design was used in the study of the efficacy, safety, and immunogenicity of ABP501 adalimumab biosimilar in patients with psoriasis. Originally, the patients were randomized at a 1:1 frequency to receive ABP501 or Humira®. After the first 16 weeks, patients from the Humira® arm were re-randomized 1:1 to two equal arms, one of which continued the treatment with Humira® and another one was switched to ABP501. Results from this study showed that switching from Humira® to the biosimilar did not have any negative effects on either efficacy or safety of the treatment.

Switching some patients to adalimumab biosimilar will not affect the validity of adalimumab equivalence assessment as the primary endpoint to evaluate the equivalence of BCD-057 and Humira® will be assessed at Week 16, which is before switching. Assessment of the secondary endpoints in the second study period will include not only the direct comparison between the study arms that have been receiving the same drug throughout the entire study but also the comparison of these study arms with the crossover arm. Thus, switching some patients from the original adalimumab to the biosimilar will provide additional information about the study drug, particularly will demonstrate the effect of drug switching on the efficacy and safety of adalimumab therapy.

Therefore, the proposed study design is justified from both scientific and practical points of view. The design meets the EMA's *Guideline on Similar Biological Medicinal Products Containing Monoclonal Antibodies* [EMA/CHMP/BMWP/403543/2010, 2012] and *Guideline on Clinical Investigation of Medicinal Products Indicated for the Treatment of Psoriasis* [EMA/CHMP/EWP/2454/02 corr, 2004]. It is also consistent with available data on the mechanism of action, contraindications, and adverse effects of Humira®.

### ***1.5.2. Description and justification of route of administration, doses, dosing regimen and treatment course***

The patients will receive adalimumab (BCD-057 or Humira®) subcutaneously according to the following regimen: 80 mg on Day 1 of Week 0 (starting dose) and then 40 mg on Day 1 of Week 1,

---

 BLA 761024 ABP 501, a proposed biosimilar to Humira (adalimumab) FDA Briefing Document Arthritis Advisory Committee Meeting July 12, 2016

Week 3, Week 5, Week 7, Week 9, Week 11, Week 13, Week 15, Week 17, Week 19, Week 21, Week 23, Week 25, Week 27, Week 29, Week 31, Week 33, Week 35, Week 37, Week 39, Week 41, Week 43, Week 45, Week 47, Week 49, and Week 51. The patients will be followed up until Week 55.

The dose and method of administration (SC injection) of BCD-057 agrees with the recommendations presented in the Russian IMU for the marketed originator Humira® (MA JIC-002422 of February 28, 2011) for the treatment of moderate-to-severe plaque psoriasis. These recommendations are based on the efficacy and safety data from the largest controlled clinical studies of various doses of Humira® in patients with moderate-to-severe plaque psoriasis. Two of three pivotal studies used the same dose and dosing regimen as those used in this study. Another Humira® clinical study in psoriasis used 2 regimens of adalimumab administration: Patients of Arm 1 received adalimumab 80 mg at Week 0 as a starting dose followed by 40 mg every other week (starting from Week 1). Patients in Arm 2 received adalimumab 80 mg at Week 0 and adalimumab 80 mg at Week 1 followed by adalimumab 40 mg weekly. The proportion of patients with PASI 75 response at Week 12 was 53% in Arm 1 and 80% in Arm 2. Thus, the treatment efficacy was higher in patients who received adalimumab according to the intensified regimen [1]. However, Arm 2 demonstrated the higher frequency of adverse events than Arm 1 (any AEs were reported in 78.0% vs. 62.2%, respectively). Thus, for better safety of adalimumab, it was decided to use the following regimen: 80 mg at Week 0 as a starting dose followed by 40 mg every other week (starting from Week 1).

Thus, the method of administration, dose, and dosing regimen are justified and agree with the study objectives. This dosing regimen for BCD-057 also meets the recommendations for the use of the original in patients with moderate-to-severe plaque psoriasis as described in the Russian Humira® Instruction for Medical Use (JIC-002422 of February 28, 2011) and the official data presented on the FDA's website [6].

### ***1.6. Clinical study compliance with regulatory requirements***

This clinical study will be conducted in accordance with the Protocol. The clinical study was developed in compliance with the GCP principles, current law and regulatory requirements of the participating countries.

### ***1.7. Description of study population***

Men and women of 18 to 75 years old with definite moderate-to-severe plaque psoriasis that was diagnosed at least 6 months before signing the informed consent. This study does not involve patients who have already received adalimumab or any other TNF alpha blockers and patients who have already received two or more biologics for the treatment of psoriasis.

## **2. Study objective and goals**

### **2.1 Study objectives**

#### ***Primary study objective:***

- To investigate the efficacy and safety of BCD-057 versus Humira® in patients with moderate-to-severe plaque psoriasis diagnosed at least 6 months before signing the informed consent form.

#### ***Secondary objectives:***

- To compare the efficacy of BCD-057 and Humira® by evaluating the proportion of patients who achieve a PASI 75 response, the changes in the BSA.
- To study the steady-state pharmacokinetics parameters BCD-057 and Humira® in a limited population.
- To assess the safety and immunogenicity of BCD-057 versus Humira®.

### **2.2 Study goals**

1. To determine the proportion of patients achieving PASI 75 response at Week 16, by study arms.
2. To determine the proportion of patients achieving PASI 75 response at weeks 24, 33, and 55, by study arms.
3. To determine the proportion of patients achieving PASI 50/90 response at weeks 16, 24, 33, and 55, by study arms.
4. To assess changes from baseline in PASI score (%) at weeks 16, 24, 33, and 55, by study arms.
5. To determine the proportion of patients achieving a reduction in the sPGA score to “complete clearance” (score 0) or “minimal disease” (score 1) at weeks 16, 24, 33, and 55, by study arms.
6. To assess changes from baseline in the affected body surface area (BSA) at weeks 16, 24, 33, and 55, by study arms.
7. To evaluate the improvement from baseline in the nail psoriasis severity index (NAPSI) at weeks 16, 24, 33, and 55, by study arms.
8. To assess change from baseline in the itch severity (VAS score from 0 to 100 mm) at weeks 16, 24, 33, and 55, by study arms.
9. To determine the key PK parameters ( $AUC_{\tau,ss}$ ,  $C_{av,ss}$ ,  $C_{max,ss}$ ,  $C_{min,ss}$ ,  $C_{trough}$ ) of adalimumab at steady state. Limited population (180 patients total, which includes 90 patients from the BCD-057 arm and 90 patients from the Humira® arm).
10. To assess changes from baseline in the quality of life (DLQI and SF-36) at weeks 16, 24, 33, and 55, by study arms.

11. To determine the proportion of patients developing binding/neutralizing anti-adalimumab antibodies, by study arms. To determine whether there is a correlation between the presence of neutralizing antibodies and the therapeutic efficacy of BCD-057/Humira®.
12. To determine the proportion of patients with treatment-emerging AEs/SAEs, by study arms.

### **3. Study hypothesis**

This clinical study is based on the hypothesis that

The clinical efficacy of BCD-057 defined as the proportion of patients with PASI 75 response at Week 16 is equivalent to the clinical efficacy of the original Humira®.

## 4. Study design

### 4.1. Primary and secondary outcome measures to be assessed in the study

#### 4.1.1 Primary endpoint

- The proportion of patients with a 75% or greater PASI improvement (reduction) from baseline (PASI 75) at Week 16.

#### 4.1.2 Secondary endpoints

##### *Efficacy endpoints:*

- Changes from baseline in PASI (%) at weeks 16, 24, 33, and 55, by study arms.
- The proportion of patients with a 75% reduction from baseline in psoriasis area and severity (PASI 75 response) at weeks 24, 33, and 55.
- The proportion of patients with a 50% and 90% PASI reduction from baseline at weeks 16, 24, 33, and 55.
- The proportion of patients with sPGA score reduced to 0 (complete clearance) or 1 (minimal disease) at weeks 16, 24, 33, and 55.
- Changes from baseline in affected BSA (%) at weeks 16, 24, 33, and 55.
- Changes from baseline in NAPSI (%) at weeks 16, 24, 33, and 55.
- Change from baseline in the itch severity (VAS score from 0 to 100) at weeks 16, 24, 33, and 55.
- Changes from baseline in health-related quality of life (DLQI and SF-36 scores) at weeks 16, 24, 33, and 55.

##### *Safety endpoints:*

- The proportion of patients who developed AEs/SAEs that, in the investigator's opinion, are related to Humira® or BCD-057, by study arms.
- The proportion of patients who experienced grade 3/4 AEs (CTCAE v. 4.03) that, in the investigator's opinion, are related to Humira® or BCD-057.
- The proportion of patients who developed AEs potentially due to TNF $\alpha$  inhibitors, by study arms. Such AEs include infections, serious infections, opportunistic infections (infections caused by opportunistic pathogenic viruses or cellular organisms), tuberculosis, malignancies, demyelinating diseases, lupus-like syndrome, congestive heart failure, allergic reactions, injection site reactions, and CBC or blood biochemistry abnormalities.

- The proportion of patients who discontinued the study due to AEs/SAEs, by study arms.

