### ***8.3. Requirements for reports, procedures for registration and reporting AEs, and filling out AE Report Forms***

#### ***8.3.1. Documenting and Reporting AEs/SAEs***

At every visit, a record must be made whether or not any AEs occurred during the period from the previous visit. Any adverse event reported for a patient since he/she signed the ICF must be recorded in source documents and in an Adverse Event Report Form (in the CRF). AEs will be documented in accordance with the Sponsor's Manual.

AEs should be registered and numbered consecutively as they occur. Each AE is reported in an *AE Report Form*. Rules for reporting AE/SAE are described in details in the Sponsor's Manual.

Adverse events must be recorded regardless of their seriousness and causal relationship with the study therapy. If an adverse event re-emerges, it must be recorded as a new AE and assigned a new number.

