#### ***Safety:***

- ECG findings.
- Urinalysis results.
- The proportion of patients who experienced AEs that, in the investigator's opinion, are related to Humira® or BCD-057.
- The proportion of patients who experienced grade 3/4 AEs (CTCAE v. 4.03) that, in the investigator's opinion, are related to Humira® or BCD-057.
- The proportion of patients in each study arm who experienced AEs potentially due to TNF $\alpha$  inhibitors. These AEs include infections, serious infections, opportunistic infections (infections caused by opportunistic pathogenic viruses or cellular organisms), tuberculosis, malignancies, demyelinating diseases, lupus-like syndrome, congestive heart failure, allergic reactions, injection site reactions, and CBC or blood biochemistry abnormalities.
- The proportion of patients who discontinued the study due to AEs/SAEs, by study arms.

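### No safety endpoint is the all-cause AE/SAE proportion that goal 12 states: the only overall AE/SAE and grade 3/4 proportions count investigator-judged related events alone

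*Protocol*

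**What the plan says.** Section 2.2, goal 12, repeated in the synopsis, reads: "To determine the proportion of patients with treatment-emerging AEs/SAEs, by study arms". It contains no reference to the investigator's view of cause.

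Section 4.1.2 then lists four safety endpoints, and the synopsis and section 8.1.2 list the same four:

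1. "The proportion of patients who developed AEs/SAEs that, in the investigator's opinion, are related to Humira® or BCD-057", by arm.
2. "The proportion of patients who experienced grade 3/4 AEs (CTCAE v. 4.03) that, in the investigator's opinion, are related to Humira® or BCD-057".
3. The proportion with AEs regarded as possible effects of TNF-alpha inhibitors, defined by a list of event types: "Such AEs include infections, serious infections, opportunistic infections", followed by tuberculosis, malignancies, injection site reactions, laboratory abnormalities and others.
4. "The proportion of patients who discontinued the study due to AEs/SAEs, by study arms" (the synopsis omits the reference to arms).

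The categorical safety data in section 9.1 repeat the filter: "The proportion of patients who experienced AEs that, in the investigator's opinion, are related" to one of the two products. That item names AEs only, where sections 4.1.2 and 8.1.2 name AEs and SAEs.

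On collection, section 8.3.1 is unrestricted: "Adverse events must be recorded regardless of their seriousness and causal relationship with the study therapy". Section 8.2.2 describes the safety evaluation as resting on how often, and in what pattern, AEs and SAEs occur in the therapy arms, again with no causality condition. It does not express this as a proportion or an endpoint.

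**The concern.** Safety is part of the primary objective (section 2.1), and goal 12 is the one goal that turns it into a quantity. A trial comparing a biosimilar with its originator asks whether the arms differ. Under randomisation and blinding, the count of all events by arm answers that directly. A related-events proportion answers a different question, because it depends on an individual causality judgement for each event.

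The protocol's own background uses all-cause figures. Section 1.5.2 compares two adalimumab regimens on any AE (78.0% against 62.2%). Section 1.3.2.3 reports any-AE rates of 62.2% (M03-656, Period A) and 73.8% (M04-716) on adalimumab. A related-events proportion from this trial could not be set beside those rates. If the endpoint lists are carried out exactly as written, goal 12 has no endpoint that reports it, although the data to do so are in the database.

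**Working it through.** The protocol gives no figure to reproduce here, and the point does not depend on sample size, alpha or margin. The check compares goal 12 with each endpoint.

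**Step 1. What goal 12 requires.** A proportion of patients, by arm, with any treatment-emergent AE or SAE, irrespective of cause.

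**Step 2. Each endpoint against that requirement.**

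| Endpoint (4.1.2, 8.1.2, synopsis, 9.1) | Limited to events judged related? | Covers all AEs/SAEs? |
|---|---|---|
| 1. Overall AE/SAE proportion | Yes | No, related only |
| 2. Grade 3/4 AE proportion | Yes | No, related and grades 3 and 4 only |
| 3. Listed TNF-inhibitor event types | No | No, listed types only |
| 4. Discontinuation due to AEs/SAEs | No | No, only events that end participation |

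**Step 3. Count.** Two of four carry the filter, two of four do not, and none of the four is the goal 12 proportion. Endpoints 3 and 4 together do not fill the gap: an event that is off the list and does not lead to discontinuation enters neither, and it enters endpoint 1 only if the investigator calls it related.

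**Step 4. Does another section define the missing endpoint?** Section 8.2.2 has the right scope (AEs/SAEs by arm, no causality filter) but names no proportion, and its statement does not reappear in the section 9.1 list. Section 8.3.1 governs recording, not analysis. So the intention and the data are present, and the endpoint is not.

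**Step 5. Grade 5.** Read literally, endpoint 2 stops at grade 4. Section 8.1.1.2 makes death a seriousness criterion, so a fatal event judged related can count under endpoint 1. The same section has deaths recorded and reported whether or not they are tied to an AE. The gap is in the wording of the severity endpoint alone.

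**The case against.** The strongest reply is that all-cause safety is already intended. Section 8.2.2 looks at AE/SAE frequency by arm, section 8.3.1 records everything, and section 8.3.1 also has every event of CTCAE grade 2 or higher registered. Section 9.1 analyses laboratory values and vital signs with no causality filter. All-cause AE tables by arm are commonly specified in a statistical analysis plan, which is not shown here, and the section 9.1 list is introduced as what the data include, not as a closed list. Much of this stands. It shows that an all-cause comparison is possible and probably expected, and it keeps the consequence modest. It does not remove the mismatch, because the protocol itself states the goal and then fixes endpoints, in four places, that do not match it.

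A reader might infer that every safety comparison between arms is confined to related events. The documents do not support that. Endpoint 3 is defined by event type and includes infections, which section 1.4.2 names as the most common AEs. Endpoint 4 has no relatedness condition.

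A reader might also infer that deaths drop out. They do not, for the reasons in the grade 5 check.

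A third inference is that the filter favours one product, or that an unexpected biosimilar-specific event would tend to be called unrelated. Causality is judged under double-blinding (section 4.3.5), and nothing in the protocol says how unexpected events would be attributed. That part is conjecture and forms no part of the point.

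**Conclusion.** The point holds as a mismatch between goal and endpoints. Two of the four safety endpoints, including the only overall AE/SAE proportion and the only grade 3/4 proportion, count investigator-judged related events alone, and none of the four is the all-cause proportion that goal 12 states. It rests on the text only and needs no numerical assumption. Its weight is moderate: no data are lost, and the safety description in section 8.2.2 already points the right way.

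It is tempting to attach a loss of power to the filter, but the documents do not support one. Write *p* for the all-cause proportion in one arm and *p + d* in the other. If the same fraction *f* of affected patients in both arms has a related event, the difference shrinks from *d* to *f·d*. If instead the excess events are the ones judged related while background events are attributed at rate *f*, the difference stays at *d* on a lower base *f·p*, and sensitivity can rise. If the excess is judged unrelated, the difference vanishes. The protocol gives no attribution rate that would choose between these cases, so neither the size nor the direction of any effect on power can be stated.

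**What to change.** Add to the safety endpoints in the synopsis, section 4.1.2 and section 8.1.2, and to the categorical safety list in section 9.1, the following proportions of patients, each regardless of causality and by arm:

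- any treatment-emergent AE;
- any SAE;
- any AE of CTCAE grade 3 or higher, so that grade 5 is covered.

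The first two bring the endpoints into line with goal 12. The third removes the same filter from the severity endpoint and closes the grade 5 wording gap. Keep the related-event proportions as supportive endpoints, and leave the TNF-inhibitor event list and the discontinuation endpoint as they are.

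The cost is a few lines of protocol text and a few extra table rows. No new data, visits or patients are needed, because section 8.3.1 already has every AE recorded whatever its cause.
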